## Abstract

**Background:**

Children with autism spectrum disorders (ASDs) suffer from sleep disorders to a considerable degree; however, there is no safe and effective treatment available in clinical practice. The objective of the trial is to assess the clinical effectiveness of auricular plaster therapy (APT) in treating sleep disorders in children with ASD.

**Method:**

This is a single-center, patient-assessor blind, randomized controlled trial. A total of 44 preschool children with sleep disorders with ASD will be included in this study. Eligible participants will be randomly assigned to either the auricular plaster group or the sham auricular plaster group in a 1:1 ratio. Participants in the different groups will receive APT or sham APT, respectively, for a total of 30 sessions over 30 days. The primary outcome includes the Children's Sleep Habits Questionnaire (CSHQ), while secondary outcomes include the Autism Behavior Checklist (ABC) and polysomnography (PSG) for total sleep time, sleep latency, awakening duration, and sleep structures. The CSHQ and ABC will be assessed at baseline, 10, 20, 30, 60, 90, and 120 days after randomization, whereas PSG will be assessed at baseline and 30 days after randomization. The follow-up period will be scheduled to be 60, 90, and 120 days after randomization.

**Discussion:**

The results of this study may provide evidence of the efficacy of APT, as well as offer new alternatives for the treatment of sleep disorders in children with ASD.

**Trial registration:**

CHiCTR.org.cn (ChiCTR2100048257). Registered on July 5, 2021.

## Introduction

Autism spectrum disorder (ASD) is a complex developmental condition characterized by difficulties in social interaction, communication, and common repetitive behavior patterns (1). Globally, the World Health Organization reported that 0.76% of children have ASD, accounting for 16% of the total number of children throughout the world (2). It is estimated that over 44% of children with ASD will develop sleep disorders, and these sleep disorders exist for a long period of time (3, 4). Sleep disorders commonly present as difficulty falling asleep, poor sleep quality, wakefulness, irregular sleep patterns, short sleep duration, and a tendency to wake up during the night (5).

As outlined by published guidelines (6–10) (Table 1), the primary treatment for autistic children with sleep disorders is to improve sleep habits. For parents of children with ASD, it will take a long time and a great deal of patience to teach children proper sleep habits, such as a comfortable sleep environment, regular bedtimes, encouraging the child to sleep alone, and avoiding naps (11). Moreover, it is unclear whether improving sleep habits could effectively treat sleep disorders in children with ASD (12).

**Table 1 T1:** Summary of clinical guidelines for the treatment of sleep disorders in children with autism spectrum disorders.

**Guidelines**	**Recommendations of treatment for sleep disorders**
2021 NICE guideline	Not mentioned
2020 AAN guideline	Behavioral strategies are first-line treatment approach (Level B). Clinicians should offer melatonin to children and adolescents with ASD if behavioral strategies have not been helpful (Level B). No evidence to support the routine use of weighted blankets or specialized mattress technology for improving disrupted sleep (Level B).
2017 BAP guideline	Melatonin, if possible, in combination with a behavioral intervention (Strength of recommendation: A). Prolonged use of benzodiazepines and related GABA agonists is not recommended (Strength of recommendation: S).
2017 NICE guideline	Not mentioned
2013 NICE guideline	Not mentioned

NICE, National Institute for Health and Care Excellence; ASD, autism spectrum disorders; AAN, American Academy of Neurology; BAP, British Association for Psychopharmacology; GABA, gamma-aminobutyric acid.

After reviewing currently published randomized controlled trials (RCTs) for sleep disorders in children with ASD, we found that these studies had several limitations: relatively small sample sizes (<40 participants), a less rigorous study design (unblinding method), and adopted different diagnostic criteria for ASD (12–25) (Table 2). The only drug currently available in children with ASD is melatonin, which regulates circadian rhythms and improves sleep (26). The first RCT on melatonin, with 11 participants, showed benefits for sleep disorders in children with ASD (25). Another trial concluded that melatonin had efficacy for sleep disorders only for a short duration (22). In 2021, Hayashi et al. (13) conducted an RCT of melatonin in 196 children and reported that melatonin was effective in treating sleep disorders in children with ASD. Nevertheless, melatonin was also associated with some adverse events (AEs), including nervous system disorders, infections and infestations, and pharyngitis. According to the 2020 American Academy of Neurology guideline, melatonin has not been clinically evaluated for safety, and its potential role in decreasing sleep disorders in children with ASD is dubious (11, 18). Moreover, taking melatonin has some potential side effects, such as enuresis, headache, and dizziness (11, 27). Other complementary alternative medicines to treat sleep disorders in children with ASD, such as aquatic exercise (14), ferrous sulfate (16), carnosine (17), weighted blanket (20), lack evidence-based recommendations, and thus remain controversial (11).

**Table 2 T2:** Randomized controlled trials of sleep disorders in children with autism spectrum disorders.

**References**	**Country**	**Center**	**Intervention group**	**Control group**	**Sample size**	**Blinding**	**Primary outcomes**	**Conclusion**
Hayashi et al. (13)	Japan	Multicenter	Melatonin	Placebo	196	Double blind	Sleep onset latency	Melatonin is effective for sleep disorders.
Ansari et al. (14)	Iran	Single	Aquatic exercise	None	40	Not mentioned	CSHQ	Aquatic exercise may improve sleep quality and reduce the serum IL-1β and TNF-α.
Papadopoulos et al. (15)	Australia	Single	Sleep behavioral intervention	Usual clinical care	61	Not mentioned	CSHQ	A brief behavioral sleep intervention can improve sleep problems.
Reynolds et al. (16)	USA	Single	Ferrous sulfate	Placebo	20	Double blind	Bedtime and wake time	No improvement in insomnia in treated with ferrous sulfate.
Mehrazad-Saber et al. (17)	Iran	Single	Carnosine	Placebo	43	Double blind	CSHQ	Carnosine could be effective in improving sleep disorders.
Gringras et al. (18)	USA	Single	PedPRM	Placebo	125	Double blind	SND and CSDI	PedPRM is effective and safe for treatment of insomnia.
Frazier et al. (19)	USA	Single	Pre-STS mattress	After-STS mattress	45	Double blind	Sleep diary	STS could improve sleep duration and sleep efficiency.
Gringras et al. (20)	USA	Single	Weighted blankets	Placebo	73	Not mentioned	TST	The use of a weighted blanket does not help children with ASD sleep.
Johnson et al. (21)	USA	Single	BPT program for parents	Not BPT	40	Not mentioned	Treatment fidelity checklist	BPT has a certain effect on sleep disorders.
Cortesi et al. (22)	Italy	Single	CBT and melatonin	Melatonin or Placebo	160	Double blind	Sleep variables*	In the short term, CBT and melatonin have efficacy for sleep disorders
Adkins et al. (12)	USA	Single	Sleep education to parents	No sleep education	36	Not mentioned	Changes in sleep latency	The sleep education pamphlet did not improve sleep latency.
Wright et al. (23)	UK	Single	Melatonin	Placebo	22	Double blind	Sleep variables^†^	Melatonin improved sleep latency and total sleep but not number of night awakenings.
Wirojanan et al. (24)	USA	Single	Melatonin	Placebo	12	Double blind	Sleep variables^‡^	The efficacy and tolerability of melatonin treatment for sleep problems can be affirmed.
Garstang and Wallis (25)	UK	Single	Melatonin	Placebo	11	Double blind	Sleep variables¶	Melatonin was beneficial for sleep disorders.

CSHQ, children's sleep habits questionnaire; TNF, tumor necrosis factor; PedPRM, prolonged-release melatonin minitablets; SND, sleep and nap diary; CSDI, composite sleep disturbance index; STS, sound-to-sleep; TST, total sleep time; BPT, behavioral parent training; CBT, cognitive behavioral therapy.

^*^Represents sleep latency, total sleep time, wake after sleep onset, and the number of awakenings in sleep variables.

^†^Represents sleep latency, total sleep, and night awakening in sleep variables.

^‡^Represents sleep-onset time, total night sleep duration, sleep-onset latency time, and the number of night awakenings in sleep variables.

¶Represents sleep latency, number of awakenings, and total sleep duration in sleep variables.

As a part of traditional Chinese medicine (TCM), acupuncture is a vital component with a long history of treating diseases such as mental illness (28–30), cardiovascular disease and cerebrovascular disease (31), and tumor disease (32, 33). Auricular therapy is one treatment modality of acupuncture, which involves stimulating specific acupoints on the outer ear in an effort to promote health and wellbeing (34). As a form of auricular therapy, auricular plaster therapy (APT) is composed of a round and hard cowherb seed and a sticky adhesive tape with a size of 0.5 cm ^*^ 0.5 cm (35). Due to the non-invasive, safe, and convenient nature, once auricular plaster is affixed by the doctor, patients themselves can press and stimulate the points at the convenience of their own time. Although the mechanism by which APT treats insomnia is not fully understood, numerous studies have indicated that APT helps relieve insomnia by modulating neurotransmitter activity and affecting the nervous system (36). Several systematic reviews and meta-analyses of APT show that APT appears to be an effective and safe treatment for patients with primary insomnia (37–41). In the most recent study, a retrospective cohort study of APT treatment of 84 patients with coronavirus disease 2019 (COVID-19) with insomnia showed that APT was effective in alleviating insomnia and anxiety (42). Another RCT of 50 patients receiving methadone maintenance treatment (MTT) showed that APT combined with electroacupuncture could significantly improve sleep quality, sleep latency, and increase MMT adherence (43). In addition, the application of APT has also been extended to the treatment of pain management (44, 45), postoperative rehabilitation (46), attention deficit (47), primary dysmenorrhea (48), and other conditions. Nevertheless, to our knowledge, there have been no RCTs evaluating the efficacy of APT for sleep disorders in children with ASD. Given that APT is effective in treating insomnia in adults, we aim to test the safety and efficacy of auricular plaster therapy for the treatment of sleep disorders in preschool children with ASD, which may provide a viable alternative treatment method.

## Methods and analysis

### Study design

This study is a parallel-design, patient-assessor blind randomized controlled trial (RCT) comparing the use of APT with sham APT. The recruitment of participants will take place from 1 August 2021 to 31 December 2022. The program will enroll autistic preschoolers with sleep disorders who will be assessed at the Sichuan Beidouxing Rehabilitation Service Center as well as three other community hospitals (Fuqin Community Health Service Center, Tiaodenghe Community Health Service Center, and Xianqiao Community Health Service Center). The clinical trial was registered on CHiCTR.org.cn (ChiCTR2100048257) before we enrolled our first participant, and the study was approved by the Second Affiliated Hospital of Chengdu Medical College, China National Nuclear Corporation 416 Hospital Ethics Committee (KJ2021012).

Eligible participants will be randomly assigned to the APT group or the sham APT group on a 1:1 basis. An observation period of 120 days will be conducted, including a 30-day treatment period and a 90-day follow-up period. Children will receive APT continuously for 1 month. Assessments will be conducted at baseline as well as 10, 20, 30, 60, 90, and 120 days after randomization. The study flowchart is shown in Figure 1, and the schedule of the trial is shown in Table 3.

**Figure 1 F1:**
[figure not shown]
Study flowchart.

**Table 3 T3:** Study schedule of the trial.

	**Study period**							
	**Enrollment**	**Allocation**	**Post-allocation**				**Follow-up period**		
**Timepoint (days)**	**-7**	**0**	**1**	**10**	**20**	**30**	**60**	**90**	**120**
**Enrollment**									
Eligibility screen	**X**								
Informed consent	**X**								
Allocation		**X**							
**Interventions**									
Auricular plaster									
Sham auricular plaster									
**Assessments**									
CSHQ			**X**	**X**	**X**	**X**	**X**	**X**	**X**
ABC			**X**	**X**	**X**	**X**	**X**	**X**	**X**
PSG			**X**			**X**			
AEs				**X**	**X**	**X**			

CSHQ, Children's Sleep Habits Questionnaire; ABC, Autism Behavior Checklist; PSG, polysomnography; AES, adverse events.

The protocol complies with the Standard Protocol Items: Recommendations for Intervention Trials (SPIRIT) guidelines (49). The Consolidated Standards of Reporting Trials (50) as well as the Standards for Reporting Interventions in Clinical Trials of Acupuncture (51) provide a framework for designing this clinical trial.

### Participants

We will include preschoolers who meet the diagnostic criteria for autism and sleep disorders. Upon meeting the inclusion criteria and not meeting any of the exclusion criteria, an ASD child will be considered eligible.

#### Inclusion criteria

Participants who meet all of the following inclusion criteria will be included: (1) meet the diagnostic criteria for sleep disorders (ICSD-3) (52) and autism (1); (2) aged 2–6 years old; (3) did not receive relevant treatment measures 1 week prior to enrollment; and (4) written informed consent obtained from parents.

#### Exclusion criteria

Participants who meet any of the following criteria will be excluded: (1) known severe cardiovascular, cerebrovascular, liver, kidney, blood, and other systemic diseases; (2) known history of Asperger's syndrome, Heller syndrome, Rett syndrome, specific receptive language disorder, or childhood schizophrenia before (53–55); (3) known taking part in other clinical trials.

#### Drop-out criteria

Participants drop out for the following reasons: (1) they experience severe adverse events (SAEs) and are ineligible for further study; (2) they withdraw from the clinical study; and (3) they have manifestations of allergies to auricular plaster.

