### Adverse events and safety assessment

The AEs included allergies to auricular plaster, swelling, and severe pain. When SAEs occur that pose a threat to the participant's safety, the study will be stopped immediately and the blinding will be canceled to preserve the participant's life. A detailed record of all AEs/SAEs will be kept during the course of the study, including the date, duration, treatment measures, and results.

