### Statistical analysis

An analysis of the data will be conducted using SPSS (Version 24, IBM, Armonk, New York, USA). Data will be analyzed on the basis of intention-to-treat (ITT) and per-protocol (PP) analysis. The ITT analysis includes all the participants who received at least one acupuncture treatment and one assessment of the primary outcome. The PP analysis includes participants who complete the trial. Continuous data will be expressed as medians and interquartile ranges. Categorical data will be presented as numbers and percentages. Continuous variables will be compared using the independent-sample *t-*test or the Mann–Whitney *U*-test. Categorical variables will be compared with the chi-squared test or Fisher's exact test. Missing values will be addressed by multiple imputations, having appropriately explored the missingness mechanism and in accordance with good practice. Two-sided *P* < 0.05 will be considered significant.

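### Children who react to the plaster drop out on the same footing as those who withdraw, with no stated provision for assessing them further, so later outcomes may be missing for treatment-related reasons

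*Protocol article*

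**What the plan says.** The Drop-out criteria section gives three reasons under one consequence:

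- "they experience severe adverse events (SAEs) and are ineligible for further study";
- withdrawal from the study;
- "they have manifestations of allergies to auricular plaster".

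The SAE reason carries a condition. The allergy reason carries none.

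Adverse events and safety assessment treats the same reaction as a safety outcome: "The AEs included allergies to auricular plaster, swelling, and severe pain". For SAEs that threaten a participant's safety, it adds that "the study will be stopped immediately and the blinding will be canceled".

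Statistical analysis plans both ITT and per-protocol analyses. On the sets it says "The ITT analysis includes all the participants who received at least one acupuncture treatment and one assessment of the primary outcome" and "The PP analysis includes participants who complete the trial". On gaps in the data it says "Missing values will be addressed by multiple imputations, having appropriately explored the missingness mechanism". Sample size allows for 10% dropout.

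Outcome measurements and Table 3 place the CSHQ and ABC at baseline and days 10, 20, 30, 60, 90 and 120, and PSG at baseline and day 30. Neither says what happens to these visits once a child has stopped the plaster.

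**The concern.** Stopping a treatment and leaving a trial are different events. An ITT comparison needs outcomes from children who stop treatment, because they are part of the effect of being assigned to it. Here a reaction to the plaster has the same stated consequence as a family's decision to withdraw.

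If staff read it that way, the child's later questionnaires are not collected and the values are imputed. The reason for the gap is then tied to treatment. The arms also differ in exposure: APT children wear seeded plasters pressed three times a day, while sham children wear unseeded plasters and are not told to press them. Reactions could therefore differ in number, or in what follows them, between the arms. Imputation that draws mainly on children who tolerated the plaster would then credit APT with a benefit that the children who stopped may not have had.

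**Working it through.** **Does dropping out mean loss of outcomes?** The article never says so outright. Three places point that way:

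- Sample size makes an allowance for dropout, which is needed only if children who drop out lack usable outcomes.
- The per-protocol set is defined by completing the trial, which contrasts completers with those who drop out.
- The SAE reason speaks of eligibility for further study, not for further treatment.

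Nothing shown provides for assessment after a child stops. The implied reading is therefore loss of later data.

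**Are these children lost from the ITT set?** Not in general. One treatment and one primary-outcome assessment keep a child in. The first CSHQ after baseline is on day 10. A child who reacts before then stays in only if the baseline CSHQ counts as the one assessment, and every later value is then imputed.

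**The plan's own figures.** Inputs from Sample size: APT mean 40, SD 9.7, power 0.80, dropout 10%, total 44. Statistical analysis gives two-sided 0.05. The sham mean is not stated. I take the cited reference mean of 48.5, so the difference is 48.5 − 40 = 8.5.

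- Normal formula: n = 2 × [9.7 × (1.960 + 0.842) / 8.5]² = 20.4, so 21 per group. The t-test version gives 22.
- With dropout: 21/0.9 gives 24 and 22/0.9 gives 25 per group, or 48 to 50 in total.
- The stated 44 is thus the t-test number without any allowance. With a difference of 9, the normal formula gives 19, and 19/0.9 gives 22, so the mismatch depends on the unstated sham mean. It is a separate matter from this point.
- The allowance itself is 0.10 × 44 = 4.4 children. It is not split by reason.

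**Size of a possible bias (illustration).** Suppose k of 22 APT children stop after a reaction and would have scored 48.5 if measured, while the other 22 − k average 40. Suppose imputation gives those who stopped values like those who stayed. Then:

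- APT mean over all randomised = 40 + 8.5 × k/22
- difference over all randomised = 8.5 × (1 − k/22)
- bias = 8.5 × k/22

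| k of 22 | Difference, all randomised | Difference, those who stay | Bias | Power at 22 per group, all measured |
|---|---|---|---|---|
| 1 | 8.11 | 8.5 | 0.39 | 77% |
| 2 | 7.73 | 8.5 | 0.77 | 73% |
| 3 | 7.34 | 8.5 | 1.16 | 69% |
| 4 | 6.95 | 8.5 | 1.55 | 64% |

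At k = 2 the bias is 0.77/8.5, about 9% of the assumed effect. If equal numbers stopped in both arms and fell short of their arm's mean by the same amount, the errors would cancel.

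**The case against.** The strongest reply is that this is an article. Follow-up after stopping treatment may be set out in the full protocol, and the imputation model belongs in the analysis plan. The visit schedule makes no exception for children who stop. The ITT set keeps most of them, and imputation is to follow an examination of the missingness mechanism. CSHQ values from day 10 or 20, where they exist, could inform the imputation. An allergy to the adhesive could occur in either arm, and no reaction rate is given.

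Much of this stands, and it limits the point. A reader might infer four stronger things that the document does not support:

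- **That any SAE removes a child.** The criterion also requires ineligibility for further study.
- **That outcome collection is stated to stop, or that these children leave the ITT analysis.** The first is implied only. The second is contrary to the ITT definition for any child with one treatment and one CSHQ assessment.
- **That keeping them gains power.** With a difference of 8.5, t-test power is 77% at 20 per group and 81% at 22. The higher figure assumes that retained children have the full effect. If two APT children have none, power at 22 per group is 73%. The gain and the bias above rest on incompatible assumptions. The 10% allowance also covers voluntary withdrawal, which no rewording recovers.
- **That the drop-out and adverse-event sections flatly contradict each other.** The purpose given for stopping and unblinding is to protect the individual participant, so one child may be meant. The wording is loose rather than clearly in conflict.

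What the objection does not remove is the rule that is stated: an allergy of any degree is a reason for dropping out, listed beside study withdrawal. Examining the missingness mechanism in a handful of children cannot show whether their values are missing at random.

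**Conclusion.** The point holds as a weakness in a stated rule. The Drop-out criteria merge stopping the plaster with leaving the trial. Followed in the sense that the rest of the article suggests, this produces missing CSHQ and ABC values for treatment-related reasons, and imputation may not repair them.

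The size is unknown. Under the assumptions shown (sham mean 48.5, stopping in the APT arm only, no benefit in those who stop, imputed values like those of children who stay), the bias towards APT is about 0.8 points for 2 of 22 children, and 0.4 to 1.5 points for 1 to 4. The direction depends on reactions, or outcomes after them, differing by arm, which the document does not establish. The case rests on validity; no power gain is claimed. It is worth correcting because correction is cheap. Whether a reaction or an SAE should stop treatment is a clinical question and is not judged here.

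**What to change.** Divide the Drop-out criteria section into two parts.

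- **Reasons for stopping the plaster:** the present clinical reasons, unchanged. State that a child who stops remains in the trial, is assessed for CSHQ and ABC at all remaining scheduled visits, has the day-30 PSG where the family agrees, and is analysed in the assigned arm.
- **Leaving the trial:** only when consent to further data collection is withdrawn.

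In Adverse events and safety assessment, say whether the stop and the unblinding apply to the participant or to the whole trial, and reconcile this with the Drop-out criteria.

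The cost is a change of wording and a few questionnaire contacts, at visits already scheduled, with families who have stopped treatment. Some may decline, so some values will still be missing. Recruitment was under way when the article was submitted, so the change helps only children whose remaining visits are still ahead.
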